**Table 2 Tab2:**
[figure not shown]
Checklist for the schedule of enrolment, interventions, and assessments

*DMSE* Diabetes management self-efficacy, *DD* Diabetes distress

### Ethical approval and consent to participate

This study is approved by the institutional review board (IRB) of the DDUHS, Karachi, Pakistan. Written informed consent will be obtained by the PI from all the participants. Data confidentiality will be maintained by keeping all questionnaires locked in a cabinet and electronic data will be kept in a password protected computer. Only the research team will have access to data.

### Plan of analysis

All statistical analysis will be performed using SPSS version 20. Intention to treat and per protocol analysis will be performed. Descriptive statistics will be reported by computing frequencies and percentages for categorical variables and means, standard deviation and ranges (minimum and maximum) values for continuous variables. All independent variables such as demographic and clinical characteristics will be compared at baseline between the two groups. Outcome variables will be calculated by summing the scores of respective scales. Paired sample t test will be used to measure the significant difference in HbA1C, DMSE and DD scores on a pre-post analysis in each group, followed by between the groups comparison using independent sample t test after the intervention. If the data collected through DMSE, DD and HbA1C will not follow the assumption of linearity for parametric testing (paired and independent sample T tests), we will use the non-parametric counterpart such as Wilcoxon signed-rank test and Mann-Whitney test, respectively. Similarly, if we could not enroll sufficient number of the participants or if there were few cases left for the analysis due to higher number of attrition rate, and the assumption for parametric testing is violated, we will switch to the non-parametric testing. If any characteristic such as demographic or clinical was found to be significantly different between the two groups at baseline, we will adjust the analysis for that variable using multivariable linear regression. Sensitivity analysis will be run to measure effect of any missing observations on outcome of the study.

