**Methods:**

This will be two arms randomized controlled trial, conducted at national institute of diabetes and endocrinology (NIDE) in Karachi, Pakistan. A sample of 120 T2DM patients of age 30–60 years with suboptimal diabetes control will be screened through eligibility criteria and DD screening tool. Patients who fulfill the eligibility criteria and have diabetes distress will be randomized into interventional and control arm. The intervention arm will receive four education sessions (40 min each) using DCM for 4 weeks duration of enrollment. Controlled arm will receive RC. DMSE and DD will be measured using the validated Likert tools at baseline and after 3 months of enrollment. Latest results of HbA1c will be retrieved from the respective medical record files at baseline and 3 months. Change in DMSE, DD scores and HbA1c levels within groups (pre-post) and between the groups after 3 months of enrollment will be compared. Multivariable linear regression will be conducted to adjust for any potential confounders.

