### Study population

#### Inclusion criteria

Patients aged 30–60 years, visiting the diabetes clinics of NIDE, diagnosed with T2DM for at least 5 years, HbA1c levels of > 7%, and found to be positive for diabetes distress (DD) based on validated DD screening tool (section 3 of Additional file 1) will be included in the study.

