### Sample size

A study from China [17] reported mean DD score of control and intervention group at baseline as 32.77 ± 14.57 and 26.08 ± 9.92 respectively (*p* value 0.073). After six months of the intervention the respective scores were 30.09 ± 12.14 and 22.79 ± 4.95 (p value 0.014). Aiming for a higher average difference of the differences (difference of 7.30) as compared to the study from china (0.62) between the intervention and control arm (which is also clinically significant), considering 95% confidence interval and 80% power of the test to detect the given difference, the minimum sample size to achieve the objective of this study will be 88 (44 in each group). After adding attrition rate, a total of 120 subjects i.e. 60 in RC arm and 60 in DCM arm will be enrolled in this study.

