#### Independent variables

This will include age, gender, BMI, education level, occupation, marital status, time since diabetes diagnosis, time since diabetes treatment, type of treatment for Diabetes e.g. Tablets, insulin etc. use of smart phones, use of internet, monthly income and intervention (DCM or RC).

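### The between-arm t test leaves out the baseline value of each outcome and conflicts with the change contrasts stated elsewhere; baseline adjustment should be prespecified and the within-arm tests made descriptive

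*Protocol article*

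**What the plan says.** The protocol article describes the main comparison in several places.

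- **Plan of analysis, within arms:** "Paired sample t test will be used to measure the significant difference in HbA1C, DMSE and DD scores on a pre-post analysis in each group".
- **Plan of analysis, between arms:** "followed by between the groups comparison using independent sample t test after the intervention". The Mann-Whitney and Wilcoxon signed-rank tests are the fallbacks.
- **Plan of analysis, adjustment:** "If any characteristic such as demographic or clinical was found to be significantly different between the two groups at baseline, we will adjust the analysis", by multivariable linear regression. The Abstract mentions regression for potential confounders more generally.
- **Independent variables:** "This will include age, gender, BMI, education level, occupation, marital status, time since diabetes diagnosis", then treatment history, phone and internet use, income and arm. Baseline distress (DD), self-efficacy (DMSE) and HbA1c are not listed.
- **Abstract, Methods:** "Change in DMSE, DD scores and HbA1c levels within groups (pre-post) and between the groups after 3 months of enrollment will be compared".
- **Enrollment and data collection procedure:** the 3-month interview and blood test serve to look at change from baseline across the two groups.
- **Sample size:** "Aiming for a higher average difference of the differences (difference of 7.30", set against 0.62 in the cited pilot trial from China.
- **Inclusion criteria:** "HbA1c levels of > 7%, and found to be positive for diabetes distress (DD) based on validated DD screening tool".

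**The concern.** A t test on follow-up values, a t test on change scores and a baseline-adjusted comparison are different estimators. On the same data they can give different estimates and p-values. The article names the first in its analysis section and describes the second elsewhere, so the contrast that decides the trial is not settled. Three outcomes are affected.

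The planned adjustment does not fill the gap. It depends on a significance test at baseline, and no baseline outcome is among the listed covariates. Baseline HbA1c might count as a clinical characteristic, but it would still need a significant difference to enter. The pilot's baseline gap in DD (6.69, p 0.073) would not have triggered the rule.

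The paired tests raise a separate difficulty. The latest HbA1c at screening both admits the patient and serves as baseline, so the mean will tend to fall at 3 months without any effect. A significant fall in one arm and not in the other is not evidence of a difference between arms.

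**Working it through.** **Inputs.** From the Sample size section: pilot DD means (SD) at baseline, control 32.77 (14.57) and intervention 26.08 (9.92), p 0.073; at six months, 30.09 (12.14) and 22.79 (4.95), p 0.014; target difference 7.30; 80% power; 44 per arm. Assumed: two-sided 5% level, equal SDs at both times, and r of 0.3, 0.5 or 0.7.

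**1. The plan's own figure.** n per arm = 2 × (1.96 + 0.84)² × SD² / difference². With SD 12.14 (the pilot's six-month control SD; the article does not say which SD it used) and 7.30, this is 43.4, rounded up to 44. The pooled baseline SD of 12.46 gives 46. So 44 reproduces as a comparison of follow-up values.

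**2. What 7.30 is.** Six-month gap: 30.09 − 22.79 = 7.30. Baseline gap: 32.77 − 26.08 = 6.69. Difference of differences: 7.30 − 6.69 = 0.61 (0.62 in the article). The target labelled a difference of differences equals the pilot's follow-up gap.

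**3. Power at 44 per arm.** SD used: follow-up only, 12.14; baseline-adjusted, 12.14 × √(1 − r²); change score, 12.14 × √(2(1 − r)). Powers are from the noncentral t distribution.

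| r | Follow-up only | Adjusted SD | Adjusted power | Change SD | Change power |
|---|---|---|---|---|---|
| 0.3 | 79.6% | 11.58 | 83% | 14.36 | 65% |
| 0.5 | 79.6% | 10.51 | 90% | 12.14 | 80% |
| 0.7 | 79.6% | 8.67 | 97% | 9.40 | 95% |

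Only the ratio 7.30/12.14 = 0.60 matters, so the scoring scale does not affect these figures.

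**4. A chance baseline gap with no effect.** A two-sided p of 0.073 is z of about 1.79. Given that gap, the follow-up z statistic is approximately normal with mean 1.79r and variance 1 − r². At r = 0.3, 0.5 and 0.7 the means are 0.54, 0.90 and 1.25, and the probability of exceeding 1.96 in absolute value is about 7%, 11% and 16%.

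**5. Paired tests with no effect and no true change.** Suppose entry requires a baseline value above c SD from the population mean. The expected change is then −(1 − r) × φ(c)/(1 − Φ(c)) SD, where r is now the correlation in the unselected clinic population. At c = 0 this is −0.5 × 0.798 = −0.40 SD for r = 0.5, and −0.3 × 0.798 = −0.24 SD for r = 0.7. Simulating two arms of 44 with c from −1 to 0:

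| r | One arm's paired test significant | Exactly one of two arms significant |
|---|---|---|
| 0.5 | about 17–81% | about 27–48% |
| 0.7 | about 11–56% | about 19–49% |
| 0.9 | about 7–22% | about 13–34% |

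The between-arm t test stayed near 5% throughout. The table describes an outcome selected on its own baseline value, which here is HbA1c.

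**The case against.** The strongest reply is that the planned between-arm test is sound. A reader might infer from section 4 of the working that it is biased or has inflated error; it does not. Under randomisation its type I error is about 5% over all trials. The 7–16% figures apply only where a baseline gap as large as the pilot's arises, and one that large or larger occurs by chance in about 7% of trials per outcome. Nor does the test carry a baseline gap in full; on average it carries a fraction r of it. So one cannot say that this trial will repeat the pilot's pattern. All of this stands.

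The power loss is relative to a better analysis. The trial was sized for the follow-up test, which meets its nominal 80%, or about 90% if all 60 per arm are followed. At r = 0.3 the gain from adjustment is 3 to 4 points. This also stands, and it makes the point a recommendation rather than a defect of validity.

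On the paired tests, a reader might take the upper figures as expected for all three outcomes. The documents do not support that. DMSE is not an entry criterion. DD is selected through a separate two-item screen while the outcome is the 17-item score, so its regression to the mean should be weaker. No clinic HbA1c distribution is given, so a cut-off at the mean is only the top of the assumed range. Nor does the article say it will infer effectiveness from paired tests; its aim is comparative.

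Finally, the words about timing in the analysis section could allow a change-score test. That is possible, but it leaves the contrast unsettled, and a change score has less power than the follow-up test when r is below 0.5.

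**Conclusion.** The point holds as one of efficiency, exposure to chance imbalance, and consistency; it is not one of bias. The analysis section sets a follow-up-only t test, other sections describe change, and the conditional regression does not ensure adjustment for the baseline outcome. Adjustment would raise power from about 80% to between 83% and 97% over assumed r of 0.3 to 0.7. The spread for a change score, 65% to 95%, shows that the choice among the stated contrasts matters. These figures rest on SD 12.14, equal SDs over time and r within the trial, which may be lower than in the clinic because entry restricts the range. The paired tests cannot show a treatment effect, and for HbA1c they may be significant with no effect at a rate that depends strongly on r and on where 7% lies in the clinic distribution. Severity: should-fix.

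**What to change.** For each of DD, DMSE and HbA1c, state one between-arm analysis: a linear model of the 3-month value on arm plus the baseline value of that outcome, fitted regardless of any baseline significance test. Analyse patients as randomised. Cover missing 3-month values by the sensitivity analysis already planned, since the step from 88 to 120 allows for 1 − 88/120 = 26.7% attrition. Report the adjusted difference with its 95% CI as the treatment effect. Show within-arm changes descriptively, without p-values.

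Reconcile the Abstract, Sample size, Enrollment and data collection procedure, and Plan of analysis sections to this contrast. In the Sample size section, 7.30 should be described and justified as a follow-up difference. With SD 12.14 the 44 per arm is then slightly conservative for the adjusted model at the correlations considered here. The rank-test fallback omits baseline in the same way and should be reworded to keep the same contrast.

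The cost is one degree of freedom per model and revised wording. The baseline values are already to be collected.

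### The rule for switching from t tests to rank tests names an assumption that t tests do not have, lets the outcome data choose the main test, and moves away from the mean difference the trial is sized on

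*Protocol article*

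**What the plan says.** The Plan of analysis sets paired t tests within each arm, "followed by between the groups comparison using independent sample t test after the intervention". It then adds a rule for when the DMSE, DD or HbA1c data "will not follow the assumption of linearity for parametric testing (paired and independent sample T tests), we will use the non-parametric counterpart", naming "Wilcoxon signed-rank test and Mann-Whitney test, respectively". A second sentence covers poor enrolment or heavy attrition: if that happens "and the assumption for parametric testing is violated, we will switch to the non-parametric testing". The two conditions there are joined by *and*. No check or threshold is given, and nothing says that the choice is made before the arms are compared.

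The same section plans multivariable linear regression for any characteristic that differs significantly at baseline.

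The Sample size section rests on means: "Aiming for a higher average difference of the differences (difference of 7.30"), with "80% power of the test to detect the given difference". It takes its figures from a study in China, where at six months "the respective scores were 30.09 ± 12.14 and 22.79 ± 4.95" (control, then intervention).

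**The concern.** There are two faults in the text and one consequence.

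- **Wrong trigger.** The t tests rest on independence, on approximate normality of the differences or of the arm means, and, in the pooled form, on equal variances. Linearity is a property of a regression relation and cannot be checked for a two-group comparison. Two analysts following the sentence could reach different tests.
- **Test chosen from the outcome data.** If normality is what is meant, the choice between a mean-based and a rank-based result for all three outcomes is made once the scores are in.
- **Change of question.** Mann-Whitney asks whether scores in one arm tend to exceed those in the other. It stands in for a comparison of means only when the arms have the same spread and shape. If they do not, a significant rank test can occur with no mean difference, and a real mean difference can be missed. Where the regression is also run, the adjusted and unadjusted results would answer different questions.

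**Working it through.** **1. What the trial is sized on.** The inputs from Sample size are a difference of 7.30, 80% power and 95% confidence, taken here as two-sided 5% because sidedness is not stated. The common SD is not stated either; 12.14, the control SD at six months, reproduces the figure:

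n per arm = 2 × (1.96 + 0.8416)² × 12.14² / 7.30² = 15.70 × 147.38 / 53.29 = 43.4, rounded up to 44.

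Power at 44: √(44/2) × 7.30/12.14 − 1.96 = 2.82 − 1.96 = 0.86, and Φ(0.86) = 80.5%.

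The stated 44 per group is therefore a comparison of means. The 7.30 equals 30.09 − 22.79.

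**2. Are unequal spread and skew plausible?** The six-month SDs differ by a factor of 12.14/4.95 = 2.45. DD has 17 items scored 1 to 6, and the Plan of analysis sums them, so the floor is 17. The cited intervention mean lies only 22.79 − 17 = 5.79 above it. Skew and unequal spread are plausible, but the article gives no distribution shape.

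**3. Error rates with equal true means.** There were 20,000 simulated trials per row, tested at two-sided 5%. Gamma and lognormal scores start at 17. For gamma with mean m and SD s, shape = ((m − 17)/s)² and scale = s²/(m − 17). At m = 30.09 this gives shape 1.16 for SD 12.14 and 6.99 for SD 4.95. Mean 51 is 3 × 17, the distress threshold in the measurement section on the summed scale. The shapes and the common means are assumptions.

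| Scenario | Welch, n=44 | Mann-Whitney, n=44 | Welch, n=60 | Mann-Whitney, n=60 |
|---|---|---|---|---|
| Both arms gamma, mean 30.09, SD 12.14 | 4.8% | 5.0% | 4.9% | 5.0% |
| Normal, mean 30.09, SD 12.14 v 4.95 | 5.1% | 6.5% | 5.1% | 6.5% |
| Gamma, mean 51, SD 12.14 v 4.95 | 5.1% | 10.6% | 5.3% | 12.5% |
| Lognormal, mean 51, SD 12.14 v 4.95 | 5.4% | 14.6% | 5.6% | 17.9% |
| Gamma, mean 30.09, baseline SDs 14.57 v 9.92 | 5.0% | 19.8% | 5.1% | 24.9% |
| Gamma, mean 30.09, SD 12.14 v 4.95 | 6.0% | 35.3% | 5.6% | 44.9% |
| Lognormal, mean 30.09, SD 12.14 v 4.95 | 6.9% | 44.2% | 6.4% | 55.3% |

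Repeat runs of the gamma case at mean 30 and 44 per arm gave about 35% to 36%.

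**4. How often the switch would fire.** The article names no check, so Shapiro-Wilk p < 0.05 in either arm is assumed. With SDs 12.14 v 4.95 and 44 per arm, the switch fires in practically all gamma trials at mean 30.09, in 43% at mean 51, and in 10% with normal data. The two-stage procedure then rejects in 34.9%, 9.2% and 5.9% of trials.

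**5. Direction.** In the gamma case at mean 30.09 the medians are 26.6 (SD 12.14) and 29.5 (SD 4.95), so the arm with the narrower spread ranks higher. With that arm as DCM, as in the cited study, Mann-Whitney at 44 per arm points against DCM in 34.9% of trials and in favour in 0.04%.

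**6. A real benefit.** With the same shape and SDs, 44 per arm and a true 4-point reduction in mean DD, Mann-Whitney favours DCM in about 13% of trials, while Welch rejects in about 50%. At the full 7.30 the figures are 92% and 98%.

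**The case against.** The strongest reply is that, under randomisation, an intervention with no effect at all leaves both arms with one distribution, and Mann-Whitney then holds 5%. This stands. The excess arises only when the intervention changes spread or shape while leaving the mean where it was.

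The large rates also rest on assumptions. The SD of 4.95 was observed at a mean of 22.79, not 30, and the cited arms already differed in spread at baseline (14.57 and 9.92). This trial enrols patients who screen positive for distress, who may score further from the floor. With normal data the excess is small. All of this stands, so the figures show what can happen and do not forecast it. That the switch would probably fire is not established either.

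The check and its threshold could sit in an analysis plan that is not shown. That is fair, but the wrong assumption is written in this article.

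Four stronger readings might be inferred, and the documents do not support them:

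- **Spurious claims that DCM lowers mean DD.** With the cited pattern of SDs the false rejections go the other way. They would favour DCM only if DCM had the wider spread.
- **Low enrolment alone forces a switch.** It counts only jointly with a violated assumption. The sentence adds nothing to the first trigger, which needs no enrolment shortfall.
- **The regression is lost.** The switching sentence replaces the t tests only.
- **No mean difference could be reported.** Means and SDs are planned as descriptive statistics, so it could still be computed.

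**Conclusion.** The point holds in limited form and should be corrected. Three parts need no simulation: linearity is not an assumption of either t test, the rule makes the main test depend on the collected outcomes, and the rank test does not target the mean difference behind the 44 per group.

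The size depends on shape. At 44 per arm with equal means and SDs 12.14 v 4.95, Mann-Whitney rejects in about 6.5% (normal), about 10% (gamma, mean 51) or about 35% (gamma, mean 30) of trials, against 5-6% for Welch. There is no inflation when the arms share one distribution. With the narrower spread in the DCM arm, the practical risk is a misleading result against DCM or a missed moderate benefit. These figures rest on assumed shapes, on carrying the cited SDs to equal means, and on DD analysed as a sum.

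**What to change.** Delete the switching rule, both sentences of it, and the word linearity. State one between-arm analysis of means in advance for each outcome: linear regression of the 3-month score on arm and baseline score, with robust standard errors, reported as an adjusted mean difference with a 95% confidence interval. A Welch t test is the simpler alternative. Apply it whatever the distribution or the number enrolled. Report Mann-Whitney and Wilcoxon signed-rank results only as a labelled sensitivity analysis.

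The cost is a change of wording. Baseline and 3-month scores are already collected, and the sample size does not change. Welch stayed between 4.2% and 6.9% in every equal-means scenario run.

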## Discussion

The DCM education tools focus on four different domains related to successful diabetes self-management such as 1) living with diabetes, 2) how diabetes works, 3) healthy eating and keeping active, and 4) starting insulin. DCM based education guides people with diabetes through a process with the aim of helping them understand and internalize information about their disease and generate insightful conclusions, which may then result in improved self-management decisions and actions.

The initial draft of the DCM were tested in UK on a group of 56 patients with T2DM. Out of 56, 70% rated the sessions based on DCM as very effective helping them find something that would help them in controlling their diabetes, almost all the participants reported that they would recommend the learning experience with someone diagnosed with diabetes, and 98% wanted to learn more about the Conversation Map tools [20]. A pilot phased randomized controlled trial in China evaluated the effect of education based on DCM as compared to traditional education on DD and diabetes empowerment among patients with T2DM. The study reported significant reduction in DD score and significant increase in the diabetes empowerment score at six months after enrollment into the study among the patients who received education based on DCM as compared to the control arm. The study could not find any significant change in the HbA1C level at six months of enrollment between the intervention and control group [17]. In Pakistan, a cross sectional study conducted in a tertiary care hospital of Karachi showed that the use of DCM for teaching patients with T2DM was useful in improving the knowledge, attitude and practices of the patients [21]. Besides, no other study has been conducted in Pakistan or their neighboring countries to evaluate the effectiveness of these novel tools for DMSE and DD in well-designed, sufficiently powered clinical trials.

The major limitations of this study are that it will be conducted in a single public sector tertiary care hospital of Karachi and hence generalizability might be limited to the catchment population who visit public sector hospitals for their treatment. On the other hand, important strength of this study is the use of validated tools translated in local language for the assessment of DMSE and DD. In addition, this study will also measure change in the HbA1c level at baseline and 3 months after the enrollment to further confirm the benefit of the intervention in controlling diabetes.

